## Methods

### Study design

We propose a hybrid type 3, cluster-randomized effectiveness–implementation trial in a 2 × 2 factorial design in 24 pediatric primary care practices across Pennsylvania. After all sites receive Standard REP, they will be randomized to one of four conditions: (1) Standard REP only (continued technical assistance), (2) TEAM, (3) LEAD, or (4) TEAM + LEAD. Figure 1 outlines the trial design. Care teams will deliver DOCC to 25 children with elevated behavioral problems and their caregivers. We will collect longitudinal data from practice staff and caregivers. SPIRIT, CONSORT, and TIDieR checklists [113–115] are in Supplemental File 1, and CONSORT flow diagrams are in Supplemental File 2. All procedures were approved by the University of Pittsburgh Institutional Review Board.

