### Implementation conditions and strategies

The four implementation conditions are shown in Fig. 1. Table 1 lists the mechanisms of change at the individual, team, and practice levels targeted by each condition. Supplemental File 3 shows the ERIC implementation strategies included within each condition and their hypothesized mechanisms of action (Supplemental Table 1) and the specific actions within each condition (Supplemental Table 2).

**Table 1 Tab1:** Implementation conditions and targets by level

Level	Implementation condition	Target/mechanism
Individual provider	Standard REP	Self-efficacy
		Attitudes
Care team	TEAM facilitation	DOCC skill
		Fidelity
		Affective, behavioral, and cognitive functioning
		Team effectiveness
Practice	LEAD facilitation	Implementation climate
		Implementation leadership

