### Power and sample size

Our power calculations for Aim 1 are based on comparisons of provider and patient outcomes among the six practices in each of the four conditions in the factorial design. For our primary implementation outcome (number of DOCC sessions), we estimate 80% power to detect an effect size (ES) of 0.42. Given our modest practice sample size, we will explore group differences in practice-level CCM core competencies. In our prior trial, large ESs were found for provider changes in behavior management practices (*ES* = 0.78) and perceived competencies (*ES* = 0.77) [107]. For patient outcomes, we assume an ICC of 0.01 in cases treated by the same provider and 20% attrition based on prior work [107, 109]. In a simple RCT with 262 cases/condition, we can detect an effect size as small as 0.25. The effect size for clinical improvement in individualized targets in our prior trial was 0.60, indicating that our sample size provides adequate power to detect group differences in patient outcomes [107].

Power calculations for mediator analyses (Aim 2) are based on simulation studies [140]. Because the sample sizes per cell are modest (6 sites per condition), we are powered to detect large effects. This seems justifiable insofar as smaller effect sizes (e.g., 0.35–0.50) are of less interest given the higher cost of using more intensive combined implementation strategies. Thus, our mediational tests are powered only for a large effect size. For our moderator analyses (Aim 3), we have power 0.80 to detect small effects of *f-square* = 0.03.

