### Statistical analyses

#### Aim 1

Our primary analytical tool for Aim 1 will be a two-way analysis of variance with interaction using mixed-effects linear models for continuous outcomes and generalized linear mixed models for categorical variables. We will use an intent-to-treat approach. We will examine patterns of missingness and, if necessary, use imputation methods using available covariates [141, 142]. For exploratory analyses, we will use variable selection methods such as Lasso and elastic net to get parsimonious models that fit well. Analyses will be conducted at the end of the trial; no interim analyses are planned.

For implementation outcomes, we hypothesize that relative to REP only, TEAM, LEAD, and their interaction will significantly improve (1) the number of DOCC service encounters per case and (2) collaborative care competencies within the practice. We will test effects on outcomes at months 6, 12, 18, and 24. Fixed effects include time, condition, and practice, and random effects will account for nesting. We will conduct planned contrasts to test differences between conditions.

For patient outcomes, we hypothesize that relative to REP only, TEAM, LEAD, and their interaction will significantly improve (1) child symptom severity and (2) quality of life. Fixed effects include time and condition, and random effects will account for nesting. As exploratory analyses, we will run larger models adjusting for demographic and baseline clinical variables and assess goodness of fit.

#### Aim 2

We hypothesize that TEAM practices will show significant gains in our proposed TEAM targets (team functioning, integration/quality) and that LEAD practices will show significant gains in our proposed LEAD targets (implementation leadership, implementation climate). We will use larger models to adjust for demographic and baseline clinical variables, test goodness of fit, and compare different time periods to check model fit. We will test if the association between each condition (TEAM, LEAD) and each implementation outcome is mediated by their respective targets and explore serial mediation.

#### Aim 3

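### For the staff-rated, practice-level mediators, six practices per condition do not give Aim 2 the stated power for large effects at conventional large values, and the plan defines neither the effect scale nor the test

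*Protocol article*

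**What the plan says.** The protocol article's Study design section describes a "cluster-randomized effectiveness–implementation trial in a 2 × 2 factorial design in 24 pediatric primary care practices across Pennsylvania". A main effect of TEAM or LEAD therefore compares 12 practices with 12, and a single-condition contrast compares 6 with 6.

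The Power and sample size section attributes the Aim 2 calculation to cited simulation studies and then concludes: "Because the sample sizes per cell are modest (6 sites per condition), we are powered to detect large effects". It defends this with "This seems justifiable insofar as smaller effect sizes (e.g., 0.35–0.50) are of less interest", on grounds of the higher cost of the combined strategies, and closes: "Thus, our mediational tests are powered only for a large effect size". Earlier in the same section, for the number of DOCC sessions, it says "we estimate 80% power to detect an effect size (ES) of 0.42".

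Under Statistical analyses, Aim 2, the plan is: "We will test if the association between each condition (TEAM, LEAD) and each implementation outcome is mediated by their respective targets". Table 1 places team functioning at the care-team level and "Implementation climate" and implementation leadership at the practice level. Table 2 has these three rated by staff at 0, 6, 12, 18 and 24 months. The fourth mediator construct, integration/quality (PICS), is rated by caregivers.

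**The concern.** The sentence on Aim 2 claims a property of the design and takes the site as its unit. TEAM and LEAD are assigned by practice, and the three staff-rated targets describe a team or a practice. The strategy-to-mediator path for those targets therefore has at most 24 independent units, and more raters or more cases do not add to that number. Mediation also needs the mediator-to-outcome path, which for a practice-level mediator again rests on 24 practices. Power to show mediation cannot exceed the power of the weaker path.

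Mechanism is one of the trial's main questions. If the report carries the power statement forward, a non-significant mediation test could be taken to rule out a large mediated effect that the test would more often than not have missed.

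**Working it through.** **The plan's own figure.** There is none to reproduce. For Aim 2 the article gives no power, significance level, numerical effect, SD scale, ICC or test. What can be checked is whether the conclusion holds under stated readings of a large effect.

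**Inputs from the protocol article.** 24 practices, 6 per condition; a mean of 4.4 primary care providers, one care manager and one practice manager per practice, so 4.4 + 1 + 1 = 6.4 staff raters if the lead provider is counted among the 4.4; up to 25 caregivers per practice.

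**Assumptions.** Two-sided 5%; 80% as the meaning of powered; no direct effect; large = 0.8 SD on the first path and a partial correlation of 0.5 on the second. The article itself calls provider effects of 0.77 and 0.78 large, though these come from a prior trial and need not be on the practice scale.

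**Step 1: strategy-to-mediator path alone, practice as unit.** Noncentral t with noncentrality d × √(n/2), n practices per arm.

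- 12 v 12, 20 df: 0.8 × √6 = 1.96, critical value 2.086, power 46%. At d = 0.77 to 0.78 it is 43% to 44%.
- 6 v 6: 0.8 × √3 = 1.39, power 24% (10 df) or 26% (20 df, pooled error from the factorial model).
- d needed for 80% power: 1.20 (12 v 12); 1.80 or 1.70 (6 v 6 with 10 or 20 df).

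**Step 2: both paths (joint-significance test), by simulation.** M = a·T + e and Y = b·M + e, with T the strategy, M the practice mediator score and Y the practice outcome, and unit residual SDs. A partial correlation of 0.5 corresponds to b = 0.577, since 0.577/√(1 + 0.577²) = 0.50. The model is the two-factor model with interaction for 24 practices and one factor for 12.

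| First path a (practice SD) | Second path | 24 practices | 6 v 6 |
|---|---|---|---|
| 0.8 | partial correlation 0.5 | 29% | 7–8% |
| 1.18 | b = 0.59, unit residual SD | 51–53% | 14–15% |
| 1.5 | standardised slope 0.59 | 78–81% | about 30% |
| 1.5 | standardised slope 0.7 | 90–91% | 45% |

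The scale of b matters. At a of about 1.5, a slope of 0.59 with unit residual SD gives about 63% to 64%. Read as a standardised coefficient (residual SD √(1 − 0.59²) = 0.81), it gives 78% to 81%.

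**Step 3: the cap from the second path.** With a = 10, so that the first path is always detected, and a partial correlation of 0.5, joint power is 66% to 67% with 24 practices and about 36% with 12.

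**Step 4: effects in individual-staff SDs.** Averaging over raters shrinks the practice-mean SD to √(ICC + (1 − ICC)/6.4), so 0.8 staff SD becomes 1.80 practice-mean SD at an ICC of 0.05 and 1.14 at 0.40. A simulation with 7 staff and 25 cases per practice, mediator ICC 0.05 to 0.30 and outcome ICC 0.01 to 0.20 gave joint power from 7% to 88%. It passed 80% only with 24 practices, a mediator ICC of 0.2 to 0.3 and a second-path coefficient of at least 0.6. Every 6 v 6 case was below 50%.

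**Step 5: caregiver-rated mediator (PICS).** With 0.8 individual SD on the first path, a within-practice slope of 0.3 to 0.5 and 20 caregivers per practice, power is 96% to 100% with 24 practices and 70% to 100% for 6 v 6 (mediator ICC 0.01 to 0.20).

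**The case against.** The strongest reply is that the plan gives no number, so nothing has been shown to be wrong. The cited simulations are not available, an article commonly leaves such inputs to the full protocol, and every percentage above depends on a chosen meaning of large. This stands in part. A reader might infer that the claim fails to reproduce, or that power is below 80% under any reasonable definition. The document supports neither: there is no figure to reproduce, and 80% is reached at about 1.5 practice SD with a standardised slope near 0.6 and in some individual-SD cases. What remains is that the sentence names the site as unit and draws a positive conclusion, which fails at conventional large values for three of the four mediator constructs.

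Second, the mediators are measured at baseline, and adjustment would help. It helps the first path: at 0.8 SD and baseline correlations of 0.5, 0.7 and 0.8, power rises from 46% to about 55%, 71% and 85%. When the baseline mediator is in both models, however, it also removes between-practice variation that the second path uses, and joint power stays at about 24% to 28%. An alternative set-up for the baseline adjustment gave 36%, 47% and 57%, still short of 80%.

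Third, the text already concedes that the tests are limited to large effects and nowhere says that a null result will count against a mechanism. That is right. The misreading is a risk that the wording leaves open, and it is not something the plan commits to.

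Fourth, a reader might see a contradiction between sizing the primary outcome for 0.42 and treating 0.35 to 0.50 as of less interest. The two may be on different scales, one a between-condition effect on sessions and the other a mediation effect on an unstated metric. It is a tension in wording only.

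**Conclusion.** The concern holds for team functioning, implementation climate and implementation leadership. At 0.8 practice SD and a second-path partial correlation of 0.5, the joint test has about 29% power with all 24 practices and about 8% for a 6 v 6 contrast. No enlargement of the first path lifts it above about 67% while the second path stays at 0.5. The statement could be true only if large means paths well beyond convention, or if it is on an individual scale with favourable ICCs and a strong second path, and the article says neither.

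These figures rest on a two-sided 5% level, the practice as unit, a single follow-up wave, no direct effect and the path sizes given; the individual-SD results also rest on assumed ICCs. Repeated waves were not modelled. The point does not extend to the caregiver-rated mediator or to the primary analysis.

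**What to change.** For the staff-rated mediators, replace the two Aim 2 power sentences with the path sizes, each with its SD scale, or the indirect effect detectable at 80% power. Take these from a simulation of this design: 24 practices, 12 v 12 per factor, a practice-level mediator averaged over staff, cases nested in practice, ICC assumptions stated with a range, the mediation test named, and the baseline mediator handled as in the analysis. The percentages above should not be written into the plan, because they depend on assumed path sizes and ICCs.

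Report these indirect effects with intervals, and state that a non-significant test will not be read as absence of a large mediated effect. Give the scale of the 0.35 to 0.50 range or drop that justification, since the primary outcome is sized for 0.42.

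The cost is wording in the power section and a short simulation. Enrolment, data collection and the primary analysis do not change. The stated power for Aim 2 will probably look less favourable.

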##### Care managers (CMs)

In each practice, we will enroll the individual acting as the practice’s behavioral health resource to serve as the CM (*N* = 24). Individuals in this role may vary in professional discipline (e.g., nursing, mental health) and experience delivering psychosocial interventions. The CM will deliver DOCC in collaboration with PCPs and the care team. CMs in practices randomized to TEAM will participate in Team Facilitation.

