#### Caregivers

We will enroll up to 25 caregivers of 5–12-year-old children in each practice for a possible total of 600 caregivers. Eligibility criteria are (1) child age (5–12 years), (2) parent/guardian with parental rights, and (3) child meets clinical cutoff on 7-item externalizing problems scale of the Pediatric Symptom Checklist-17 (PSC-17) [117]. Based on prior trials, we expect to recruit more female than male caregivers and for participants to vary in race/ethnicity by practice. Our primary informant is the caregiver due to the children’s young age and ethical concerns about assessing children without face-to-face contact.

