#### Implementation outcomes

##### Services Provided Log (SPL)

After each service encounter, providers will record the type of contact (e.g., treatment session, collaborative care meeting), individuals present, intervention content, and plans for next contact [107, 108]. Our primary outcome is the number of DOCC service encounters delivered to each patient by all providers.

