##### Practice level

We will examine baseline implementation leadership (ILS) and implementation climate (ICS) as moderators of the LEAD condition.

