We will test moderation of TEAM effects by provider characteristics, moderation of LEAD effects by practice characteristics, and moderation of TEAM and/or LEAD effects on child outcomes by family characteristics. We will adapt standard tests for interaction for a detailed study of the candidate moderators. We will use Wallace et al.’s method to derive a single optimal linear combination of moderators [143]. The composite moderator typically has a larger *ES* than any one variable; the relative weights of the composite index can be interpreted to determine the relative importance of moderators for practical applications.

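### The single Aim 3 power figure (0.80 at f-square 0.03) fits family-level moderators; it is wrong for practice-level moderators of the competency outcome and depends on an unstated ICC for encounters per case

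*Protocol article*

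**What the plan says.** The power statement for Aim 3 is one sentence in the protocol article, Power and sample size: "For our moderator analyses (Aim 3), we have power 0.80 to detect small effects of" f-square = 0.03. It does not separate moderators by level or outcomes by type.

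Aim 3 names seven moderators: staff attitudes (PBS) and care manager discipline at provider level, ILS and ICS at practice level, and caregiver gender, caregiver race/ethnicity and child baseline severity at family level. Three of them bear on this point:

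- **Care manager discipline.** Each practice enrolls one person, its "behavioral health resource to serve as the CM" (N = 24).
- **ILS and ICS.** Under the Practice level heading: "We will examine baseline implementation leadership (ILS) and implementation climate (ICS) as moderators of the LEAD condition".

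The Measures heading above the moderators ties them to effects on implementation outcomes. Statistical analyses, Aim 3, directs only the family characteristics explicitly to child outcomes. There are two main implementation outcomes. Encounters are counted per case: "Our primary outcome is the number of DOCC service encounters delivered to each patient by all providers". The MHPRI is aggregated over informants to one practice total.

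Just before the Aim 3 sentence, the same section says of the mediation tests: "Because the sample sizes per cell are modest (6 sites per condition), we are powered to detect large effects".

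**The concern.** TEAM and LEAD are assigned to practices. When the moderator also takes one value per practice, the interaction is estimated from differences between 24 practices, and more cases within a practice help only as far as the ICC allows. A power figure that needs well over 200 independent observations cannot be carried over to such a moderator without an ICC, and cannot hold at all when the outcome is itself one value per practice.

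The sentence also sits badly beside its neighbor: the same six sites per condition are said to support only large effects for mediation, then small effects for moderation.

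At stake is how a null result is read. If care manager discipline or baseline leadership shows no interaction, a reader relying on the stated power could conclude that even small moderation has been ruled out. For competencies, only very large moderation would have been detectable.

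**Working it through.** **Inputs from the protocol article.** 24 practices, six per condition (Power and sample size). Cases: "We will enroll up to 25 caregivers of 5–12-year-old children in each practice for a possible total of 600 caregivers" (Caregivers). Attrition of 20% leaves 600 × 0.8 = 480 cases, or 20 per practice. The only ICC: "we assume an ICC of 0.01 in cases treated by the same provider and 20% attrition based on prior work". **Assumptions:** two-sided alpha 0.05; one tested df for a single interaction; model terms for condition, moderator and interaction (p = 3); every ICC other than 0.01.

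**Method.** Noncentral F test of the added interaction, with noncentrality λ = f² × N and denominator df N − p − 1.

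**1. The plan's own figure.** It cannot be reproduced uniquely, because its inputs are not given. With 1 df, f² = 0.03 reaches power 0.80 at N = 264 (λ = 0.03 × 264 = 7.92; power 0.801). Other case-level bases also land on it: 480 cases deflated for ICC 0.01 with 4 df give 0.801, and 600 cases at ICC 0.01 with 7 df give 0.798. All of these bases count cases.

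**2. Family-level moderators.** With 480 cases and 1 df, power at f² = 0.03 is 0.966. Deflating to 480 / (1 + 19 × 0.01) = 403.4 effective cases gives 0.935. The claim is met.

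**3. Practice-level moderator, practice-level outcome (MHPRI).** N = 24, λ = 0.03 × 24 = 0.72, denominator df 24 − 3 − 1 = 20. Power is 0.128. The f² detectable with power 0.80 is 0.3615, so the required λ is 0.3615 × 24 = 8.68. Larger models (p = 5 or 7) give 0.366 and 0.371. A simulation of 10,000 trials with a random normal moderator gives power 0.116. No ICC enters here.

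**4. Practice-level moderator, encounters per case.** Effective N = N / (1 + (m − 1) × ICC), with m = 20 (N = 480) or m = 25 (N = 600), and denominator df 20. For example, at ICC 0.05: 480 / 1.95 = 246.2 and 600 / 2.20 = 272.7.

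| Practice ICC | Power at f² = 0.03 (480 / 600 cases) | Detectable f² (480 / 600 cases) |
|---|---|---|
| 0.01 | 0.91 / 0.95 | 0.022 / 0.018 |
| 0.03 | 0.82 / 0.87 | 0.028 / 0.025 |
| 0.05 | 0.73 / 0.78 | 0.035 / 0.032 |
| 0.10 | 0.56 / 0.59 | 0.052 / 0.049 |
| 0.20 | 0.38 / 0.39 | 0.087 / 0.084 |

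**5. Break-even ICC.** Power 0.80 at f² = 0.03 needs 8.68 / 0.03 = 289 effective cases. Then ICC = (480/289 − 1)/19 = 0.035, or (600/289 − 1)/24 = 0.045.

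**6. Cross-check.** Simulating practice means with a random normal practice-level moderator gives lower power: 0.82-0.88 at ICC 0.01, 0.72-0.77 at 0.03, 0.63-0.67 at 0.05, 0.49-0.51 at 0.10 and 0.33-0.34 at 0.20. On that basis break-even lies between 0.01 and 0.03, so the formula in steps 4 and 5 is the more favorable to the plan.

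**The case against.** The strongest defense concerns the primary implementation outcome. Encounters are counted per case, and a moderator with 24 values does not by itself reduce several hundred cases to 24 observations. At the one ICC the article states, power exceeds 0.90.

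The Aim 1 figure for encounters (effect size 0.42 at 80% power) can also be used to back out an ICC. It needs 89 independent cases per arm. Read as six versus six practices, which fits the section's description of its comparisons, the implied ICC is about 0.005-0.03 and Aim 3 power is 0.87-0.93. Read as 12 versus 12, it is about 0.08-0.10 and power is 0.59-0.63. This defense stands to the extent that a reader who infers that the claim is false for all implementation outcomes goes beyond the documents. It does not establish the claim either: the ICC of 0.01 is stated for patient outcomes among cases of one provider, not for encounter counts within a practice.

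Two other stronger readings are not supported:

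- A reader might count attitudes as a fourth moderator with one value per practice. The PBS is completed by all staff, is classed as provider level, and is not said to be averaged over the practice.
- A reader might take "The composite moderator typically has a larger" effect size as a sign that the composite moderator will be reported with in-sample optimism. The article does not rule out validation, which an analysis plan may cover, and it does not state a composite of all seven moderators on one outcome.

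It is also fair to say that a journal article need not print N, alpha and ICC for each calculation, and that competencies are already exploratory. The omission is not the fault. The fault is a stated power that the design does not have for some of the analyses it covers, and labeling the outcome exploratory does not correct that sentence.

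**Conclusion.** The power sentence is wrong as written because it is unqualified.

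- **Family-level moderators:** attainable.
- **Three practice-level moderators on MHPRI competencies:** wrong. Power at f-square 0.03 is about 0.13, and the detectable value is about 0.36, roughly twelve times the stated one (0.36 / 0.03 = 12).
- **The same three on encounters per case:** unsupported without a practice-level ICC, but not shown to be false. It holds below an ICC of about 0.035 to 0.045 and fails above.

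This rests on two-sided alpha 0.05, one tested df, and ILS and ICS entering as one value per practice. Their practice-level label implies that, although staff complete them and the aggregation is not spelled out. Care manager discipline needs no such assumption. MHPRI gives 24 values per timepoint; using several timepoints changes the precision of each practice's score but not the number of practices. ICCs other than 0.01 are illustrative.

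**What to change.** In Power and sample size, restrict power 0.80 for f-square = 0.03 to the family-level moderators, and add:

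- for practice-level moderators of competencies, a detectable f-square of about 0.36;
- for practice-level moderators of encounters per case, the assumed practice-level ICC and the detectable f-square it implies: about 0.02 at ICC 0.01, 0.03-0.035 at 0.05, 0.05 at 0.10, or 0.08-0.09 at 0.20. The study team should choose and justify the ICC; these values only show the range;
- a label of exploratory for the practice-level moderator tests.

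The cost is a few sentences and a short recalculation. Design, sample size and data collection do not change.
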